### Validity and reliability/rigor

All the instruments used in this study were tested for validity and reapplicability in the Brazilian population. In addition, randomization means that there are no systematic biases regarding the subjects’ allocation, since it ensures that it is random, minimizing the influence of confounding variables. Blinding is also critical, as it controls for cointerventions and bias outcome evaluations.

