### Design

A randomized controlled trial (RCT), blinded and with follow-up (2 months after hospital discharge), designated Nursing Home Care Intervention Post Stroke (SHARE). All stages of the RCT are in accordance with the recommendations of the Consolidate Standards of Reporting Trials (CONSORT) [28]. The protocol study is in accordance with the Standard Protocol Items: Recommendations for Interventional Trials (SPIRIT) Checklist as Additional file 1 and Fig. 1.

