### Participants

The study participants will be the family caregivers selected at the time of hospital discharge at the SCU-Stroke. Family caregivers will be considered the persons responsible for the care of the stroke survivor at home. They will reorganize the home for the stroke survivor and perform most of the care. They may or may not have consanguineous ties with the stroke survivor.

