### Recruitment and randomization

The stroke survivors and their family caregivers will be selected during the hospital stay at SCU-Stroke. Those who meet the inclusion criteria and are eligible will be invited to participate in SHARE. Ethical procedures will be guaranteed and participants will be able to discontinue participation at any time in the research. Participants selected will receive a HV for baseline assessment within 7 days after discharge. Participants will be picked up, selected and evaluated by research assistants, who in order to minimize bias, will be responsible for: (1) obtaining the consent of family caregivers and the stroke survivors and (2) sending the participants baseline data for randomization.

The allocation of the participants in the IG or in the CG will be through simple randomization, through a numerical list generated by the website randomization.com. This list has a numerical order, in which each number is already assigned to one of the groups randomly. Thereafter, patients are given a number and their designation as they are included in the study. Randomization will occur after the baseline evaluation of stroke survivors and family caregivers, and will be performed by a trained research assistant who is not involved in the evaluation of the participants nor involved in the SHARE intervention.

The CG will receive conventional care, and the IG will receive the SHARE intervention. The assistant responsible for randomization will inform the interventional nurses which patients are assigned to the IG. The final evaluation of all participants will be performed by the same research assistants in the initial assessment 60 days after the date of the patient’s discharge from the hospital. The logistics of the study are presented in Fig. 2. Regarding the blindness, the trial will have outcomes obtained from blinded evaluators. Study participants will not be blind to the intervention.

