### Data collection and outcomes

#### Primary and secondary outcomes

The primary outcomes will be: the caregiver’s burden and QofL, as measured by the Caregiver Burden Scale and by the World Health Organization Quality of Life–BREF (WHOQOL-BREF)_ and the World Health Organization Quality of Life (for caregivers aged over 60 years) (WHOQOL-OLD) [32–34]. Secondary outcomes: functional capacity measured by Functional Independence Measure (FIM) [35]; the hospital readmission of the stroke survivors and the use of health care services by participants after the stroke episode. Primary outcomes and functional capacity will be measured within 1 week after discharge and 2 months after discharge. The outcomes of hospital readmission and use of health services will be evaluated 60 days after discharge (Table 1).

**Table 1 Tab1:** Outcomes and time of data collection: stroke survivors and their family caregivers

Outcome and instrument	Family caregiver vs. stroke survivors	Data collection time	
		T0 (7 days)	T1 (60 days)
Primary outcomes			
Caregiver Burden Scale	Family caregiver	X	X
World Health Organization Quality of Life (WHOQOL-BREF and -OLD)	Family caregiver	X	X
Secondary outcomes			
Functional Independence Measure (FIM)	stroke survivor	X	X
Hospital readmission (yes/no)	stroke survivor		X
Use of health care services	Family caregiver and stroke survivor		X

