### Instruments

#### Caregiver Burden Scale

The Caregiver Burden Scale was adapted and validated to the Brazilian context in 1998, obtaining intra and interobserver reproducibility coefficients of 0.87 and 0.92, respectively [32]. This scale has been used in research to evaluate the caregiver’s burden of caring for stroke patients. It has 22 items divided into five dimensions: general tension, isolation, deception, emotional involvement and environment. It addresses important areas for caregivers such as health, mental well-being, personal relationships, physical burden, social support, finances and the environment [36]. To these questions, answers from 1 to 4 can be attributed, being: 1 – not at all; 2 – rarely; 3 – sometimes and 4 – often. For the measurement of the caregivers burden, the total score is obtained by the arithmetic mean of the values equivalent to the answers of the 22 questions. There is no cut-off point to classify the burden [32].

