### Other outcomes

Hospital readmissions: yes or no?

Use of services: information will be collected by a questionnaire prepared for the study related to the health care services used by the stroke survivors and their caregivers, as well as the reason for using the services. The services expected to be commonly used by stroke survivors and family caregivers are services from the health public system such as primary health care centers, appointments with nurses and physicians, pharmacies and emergency departments. Furthermore, they may use services from the private health services such as hospitals and appointments with physicians.

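### The article calls the trial blinded and credits blinding with controlling bias, but only evaluators are blinded and both primary outcomes are self-reports by caregivers who know their arm

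*Protocol article*

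**What the plan says.** All places are in the protocol article.

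- **Design:** "A randomized controlled trial (RCT), blinded and with follow-up (2 months after hospital discharge". The section does not say who is blinded.
- **Recruitment and randomization:** "the trial will have outcomes obtained from blinded evaluators", and "Study participants will not be blind to the intervention". The assistant who randomises tells the interventional nurses which patients are in the intervention group.
- **Participants:** "The study participants will be the family caregivers selected at the time of hospital discharge at the SCU-Stroke".
- **Primary and secondary outcomes:** "The primary outcomes will be: the caregiver’s burden and QofL, as measured by the Caregiver Burden Scale", with quality of life measured by the WHOQOL-BREF and, for older caregivers, the WHOQOL-OLD.
- **Caregiver Burden Scale:** "the total score is obtained by the arithmetic mean of the values equivalent to the answers of the 22 questions".
- **Validity and reliability/rigor:** "Blinding is also critical, as it controls for cointerventions and bias outcome evaluations".
- **Discussion:** the method is described as robust. The listed limitations concern loss to follow-up and changes of caregiver; unblinded self-report is not among them.

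**The concern.** For burden and quality of life, the caregiver produces the measurement and the research assistant only collects it. If the caregiver knows the arm, an assistant who does not know it cannot take expectation or gratitude out of the answers.

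The contrast makes such a shift plausible. The intervention arm has three home visits from a pair of nurses that include emotional support, and the control arm has none. A reporting shift, if present, would most naturally favour the hypothesised direction: less burden and better quality of life.

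At stake is how a positive primary result may be read. As written, the article would let it be presented as protected by blinding, when blinding gives these two outcomes no such protection.

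**Working it through.** **Step 1: who knows the allocation, set against what blinding is said to control.**

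| Party | Knows the arm? | Source |
|---|---|---|
| Family caregivers (the participants) | Yes | Participants; Recruitment and randomization |
| Interventional nurses | Yes, informed after randomisation | Recruitment and randomization |
| Outcome evaluators | No | Recruitment and randomization |

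- *Reporting bias in burden and quality of life:* the score comes from the caregiver, who is not blind. Evaluator blinding does not reach it.
- *Cointerventions:* these depend on what caregivers and care providers do. Caregivers and interventional nurses know the arm. Evaluator blinding does not reach this either.
- *FIM:* each task is graded on seven levels, so rater judgement enters. Here evaluator blinding does help.

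The claim under Validity and reliability/rigor thus holds in part for the FIM. It fails for both primary outcomes and for cointerventions.

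**Step 2: the plan's own figure.** Inputs from Sample size: 0.9 SD, power 0.80, confidence 0.95 (taken as two-sided), 20% loss.

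n per arm = 2(1.96 + 0.84)² / 0.9² = 19.4, rounded up to 20. Adding 20% gives 20 × 1.2 = 24 per arm, or 48 in total, as stated. (Dividing by 0.8 instead gives 25 per arm, or 50.) The sample size reproduces, and this point does not change it.

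**Step 3: what a reporting shift could do (illustration only).** Assume no true effect and a shift of b SD in the intervention arm. The value of b is an assumption; the documents give none. With n completers per arm, the two-sample t statistic has 2n − 2 degrees of freedom and noncentrality b√(n/2). For n = 19 (48 × 0.8 = 38.4, so 19 per arm) and b = 0.5, the noncentrality is 0.5 × √9.5 = 1.54. Probability of rejection at two-sided 5%:

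| b (SD) | n = 19 | n = 20 | n = 24 |
|---|---|---|---|
| 0 | 5.0% | 5.0% | 5.0% |
| 0.1 | 6.0% | 6.1% | 6.3% |
| 0.2 | 9.2% | 9.5% | 10.4% |
| 0.3 | 14.7% | 15.2% | 17.5% |
| 0.4 | 22.4% | 23.4% | 27.4% |
| 0.5 | 32.3% | 33.8% | 39.6% |

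**Step 4: the 60-day visit.** Table 1 places burden, WHOQOL, FIM, readmission and service use at the same time point. The service-use questionnaire asks which services were used and why. Its examples are "primary health care centers, appointments with nurses and physicians, pharmacies and emergency departments", introduced as services of the public health system. A caregiver might mention the SHARE visits when answering, but nothing in the text says the form asks about them.

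**The case against.** **Disclosure.** The strongest reply is that the article already says who is blinded: evaluators are, participants are not. The label under Design can then be read as shorthand. It is right that nothing is concealed, and a reader who inferred concealment would be wrong. But an accurate sentence in one section does not correct an unqualified label in another or an overbroad claim in a third; it shows that they disagree.

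**Unavoidable.** Home-visit education cannot be hidden from the caregiver, and burden and quality of life are the caregiver's own experience. This stands. The point is about description and interpretation and does not ask for participant blinding. The FIM also benefits from evaluator blinding, so the bias claim should be narrowed, not deleted.

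**Assessor unblinding.** A reader might infer that the service-use questionnaire reveals the arm to the evaluator. The documents do not support that. Nurse appointments appear there as examples of public-system care, and no section says that research visits are asked about or recorded. That the same assistants return at 60 days is no exposure in itself, because their first contact precedes randomisation. Disclosure remains a possibility only.

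**Missing safeguards.** A reader might also count the lack of an interviewer script, a form order or an arm-guess item as a fault. A journal article may leave such detail to the full protocol, so its absence is not a finding.

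**Magnitude.** The table in step 3 would apply to any unblinded self-report trial of this size. That is fair: it shows sensitivity and is no estimate for this trial.

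**Conclusion.** The point holds as an error of description that affects interpretation. The article attributes to the design a protection that, by its own account of who is blinded, the two primary outcomes do not have, and it makes a cointervention claim that evaluator blinding cannot support. This follows from the text and needs no assumption.

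The size of any bias is unknown. Under an assumed shift of 0.2 to 0.5 SD with 19 completers per arm, the false-positive rate would be about 9% to 32% instead of 5%. The conclusion does not depend on these values. It would go too far to infer that a positive result would be spurious, or that evaluator blinding will fail; neither is shown.

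**What to change.** 1. **Design:** replace the bare label with *evaluator-blinded; participants and interventional nurses not blinded*.
2. **Validity and reliability/rigor:** limit the statement on outcome bias to evaluator-rated outcomes such as the FIM, and remove the claim about cointerventions.
3. **Discussion, limitations:** add that both primary outcomes are self-reported by caregivers who know their arm, so that a positive effect on burden or quality of life is reported as possibly including reporting bias.
4. **Precaution at 60 days:** complete the FIM, burden and WHOQOL before the readmission and service-use questions, and do not count SHARE research visits as service use.

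**Cost:** wording in three sections and a form order, with no added visits or staff. The trial's protection against bias will read less favourably. The Discussion says data collection is under way, so a new order could mean that earlier and later participants meet the 60-day forms in different sequences; if so, the date of the change should be recorded. Items 1 to 3 can be made whatever the state of data collection.

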## Discussion

With the aging population, stroke has increasingly affected older adults, causing functional and cognitive consequences that make these people dependent on care for their activities of daily living. Family caregivers will have to perform care activities, often in a sudden way, in addition to dealing with all the changes that this situation generates in the family organization at home. Thus, it is necessary to orientate the family caregivers to perform these activities, so as to offer support that provides greater security and knowledge, and also manages their emotions and reorganizes the family context in front of the dependent stroke survivor.

SHARE is an unpublished study in Brazil, the first one being conducted with family caregivers of older adult stroke survivors. Despite national concerns about the quality of health care, coverage and access to services, the recent proposal for home care and instrumentalization of family caregivers is still incipient. Statistically significant results are expected to demonstrate the reduction of the level of burden and the improvement of the QofL of family caregivers of the older adults stroke survivors. As a secondary outcome, it is also believed that the stroke survivors will improve their functional capacity, reducing the use of the emergency services. Furthermore, the SHARE intervention will promote the use of primary health care services, and hospital readmissions can be avoided.

Several studies have suggested the implementation of interventions that orientate family caregivers in the home context, offering education for the development of technical skills and emotional support, since these are considered more effective in reducing the burden and improving the QofL [47–51]. In addition, they also have a positive effect on reducing the use of services and hospital readmissions, since they improve the abilities of caregivers to perform the activities necessary for the adequate care of the older adults [21, 52].

In this study, outcomes were selected that demonstrate the positive effects of home interventions, both for patients and caregivers, and for the health system. The expected results provide policymakers with information for the strengthening of home care policy. This implies less use of financial resources with hospitalizations and frequent use of emergency health services, both by the stroke survivors and their family caregivers, who may also become sick without adequate support.

It is also considered that the method of this study is robust and adequate to evaluate the effect of educational intervention to family caregivers of the stroke survivors, besides offering important information for the implementation of SHARE in the context of the Brazilian health system. At the moment, the study is in the phase of data collection with an expected end in July 2017.

Possible limitations to this study may include the loss of follow-up due to the death of the stroke survivors, hospitalization in long-term institutions or caregivers exchange, as well as the hiring of formal caregivers. Despite this, the studies developed with this approach in the international context are limited and they are unpublished in the national (Brazilian) context. The present study will contribute to necessary information for future research.

From this RCT it will be possible to provide scientific arguments for the implementation of educational nursing intervention to family caregivers of stroke survivors at home. It is expected that there will be a reduction of the family caregivers’ burden, improvement in their QofL, as well as a decrease in the hospital readmission of the older adults and use of the health services of the stroke survivors and their family caregivers. In addition, this study will provide support for the strengthening of public policies directed to home care and to family caregivers of dependent stroke survivors.

### Trial status

The protocol was registered at ClinicalTrials.gov on 3 June 2016 with identification number NCT02807012. The data recruitment began in May 2016. At the moment, caregivers and stroke survivors have been recruited and the SHARE intervention has been carried out. The recruitment will be completed in December 2017.

## Abbreviations

CG: Control group
CONSORT: Consolidated Standards of Reporting Trials
FIM: Functional Independence Measure
FIPE: Fundo de Incentivo a Pesquisa e Eventos
HCPA: Hospital de Clínicas de Porto Alegre
HCS: Home care services
HV: Home visit
IG: Intervention Group
QofL: Quality of life
RCT: Randomized controlled trial
SCU- STROKE: Special Care Unit of Stroke
SHARE: Nursing Home Care Intervention Post Stroke
SPIRIT: Standard Protocol Items: Recommendations for Interventional Trials
SPSS: The Statistical Package for Social Sciences
WHO: World Health Organization
WHOQOL-BREF: World Health Organization of Quality of Life-BREF
WHOQOL-OLD: World Health Organization of Quality of Life-OLD
